# A multicentre, randomized, controlled open-label trial to compare an Accelerated Rule-Out protocol using combined prehospital copeptin and in-hospital high sensitive troponin with standard rule-out in patients suspected of acute Myocardial Infarction – the AROMI trial

**DOI:** 10.1186/s13063-018-2990-z

**Published:** 2018-12-12

**Keywords:** AMI, ACS, Rule-out, Copeptin, High-sensitivity troponin, hs-cTn, Length of stay, LOS

## Abstract

**Background:**

Suspicion of acute myocardial infarction (AMI) is among the most common reasons for admission to hospital in Denmark. Owing to this suspicion, an estimated 50,000 patients are admitted every year. Only 15–20% are finally diagnosed with AMI, whereas 40% are discharged after rule-out of AMI and without initiation of any treatment or need for further admission. In patients discharged after rule-out, the current diagnostic protocol, using consecutive troponin measurements, results in an average length of stay (LOS) of 8–12 h. This leads to overcrowding in both the emergency departments and coronary care units. Measuring copeptin and high-sensitivity cardiac troponin (hs-cTn) upon hospital arrival has shown potential for early rule-out of AMI. However, the diagnostic performance may be improved by accelerating the copeptin measurement of blood sampled already in the pre-hospital phase. Additional evidence on LOS reduction and safety of the rule-out strategy in a large cohort of all-comers is needed.

**Methods/design:**

The rule-out potential is being evaluated in a randomized controlled trial including 4800 patients admitted to hospital for suspicion of AMI. Patients are randomized to either standard rule-out (consecutive troponin measurements) or accelerated rule-out (copeptin measured in a blood sample acquired before hospital admission, combined with troponin measured in the first blood sample upon admission).

**Discussion:**

Sampling blood for copeptin analysis already in the pre-hospital phase and combining this with a later hs-cTn measurement may be the optimal timing for achieving the best diagnostic performance in an AMI rule-out protocol/strategy. Moreover, we are directly comparing pre-hospital and in-hospital blood sample results to address this issue of timing, and we also are comparing single-marker strategies with dual-marker strategies. If the combination of copeptin and hs-cTn is confirmed to rule out AMI safely, implementation of this fast rule-out protocol could optimize patient flow, reduce health care expenses and enable allocation of resources to patients with confirmed illness. In future, when point-of-care analyses of copeptin and hs-cTn are available, hospitalization of the large proportion of patients with symptoms raising suspicion of AMI could potentially be avoided.

**Trial registration:**

ClinicalTrials.gov, NCT02666326. Registered on January 24, 2016.

**Electronic supplementary material:**

The online version of this article (10.1186/s13063-018-2990-z) contains supplementary material, which is available to authorized users.

This protocol covers the full study according to Standard Protocol Items: Recommendations for Interventional Trials (SPIRIT) recommendations (*see* Fig. 1 and SPIRIT checklist in Additional file 1).

**Fig. 1 Fig1:**
[figure not shown]
Standard Protocol Items: Recommendations for Interventional Trials (SPIRIT) diagram. ^#^ Result of blood sample analysis is reported to the clinical personnel. ^¤^ No result of blood sample analysis is reported to the clinical personnel. ^(#)^ Performed depending on result of prior samples

## Background

Suspected acute myocardial infarction (AMI) constitutes one of the largest patient groups in emergency medicine, accounting for 6% of all acute health care contacts and up to 27% of medical admissions [1]. In Denmark, more than 50,000 people are hospitalized annually with suspected AMI [2]. Emergency departments (EDs) and coronary care units (CCUs) are struggling with overcrowding, and patients with suspected AMI represent a huge health care challenge [1, 3]. The majority of these patients suspected of AMI have reasons for chest discomfort other than AMI, and most are discharged without any initiation of treatment [2]. The suspicion of AMI dictates immediate emergency medical services (EMS) dispatch, emergency hospital admission, cardiac surveillance and consecutive blood sampling [4]. Thus, a huge potential lies in optimizing patient management by earlier differentiation of patients with versus without AMI.

According to the Universal Definition of Myocardial Infarction, the diagnosis of AMI requires demonstration of a rise or fall pattern of cardiac biomarkers in the blood, with at least one value above the 99th percentile [5]. Therefore, consecutive measurements of two cardiac troponin (cTn) samples at intervals of 3–6 h is the present gold standard procedure to confirm or rule out AMI [4].

The standard diagnostic procedure often results in prolonged admissions for the patients in whom AMI is ruled out, because a final decision may not be reached until results of all analyses are available. Even when a high-sensitivity cardiac troponin (hs-cTn) assay is used, the length of stay (LOS) is between 8 and 12 h for patients discharged after rule-out of AMI [6, 7]. The health care-related costs of these admissions are significant [8].

Copeptin has been suggested as an additional biomarker for diagnosing AMI [9–15]. Copeptin is a by-product of the production of arginine vasopressin (AVP), which is also known as antidiuretic hormone. AVP is part of the human endogenous stress response. It is released immediately from the pituitary gland as part of the humoral response to severe stress, including an AMI. AVP is difficult to measure and has a short half-life in blood, but copeptin is stable and easy to measure [16, 17]. In case of an AMI, copeptin is released early, reaches peak concentrations in the blood within the first hours after onset of symptoms, and returns to normal levels within 4–12 h. Thus, the release kinetics are inverse to those of cTn (*see* Fig. 2) [12, 17–19].

**Fig. 2 Fig2:**
[figure not shown]
Temporal release kinetics of troponin and copeptin in acute myocardial infarction. Release pattern of copeptin versus conventional biomarkers in the first 24 h since symptom onset. Reproduced with permission from reference [19]

Previous studies have suggested using the combination of copeptin and high-sensitivity cardiac troponin T (hs-cTnT) for fast and reliable rule-out of AMI [7, 18]. However, in the one randomized study performed so far, sample sizes were small, and the event rates were low in those where AMI was ruled out [7]. This leads to doubt about the safety of using the hs-cTnT/copeptin strategy rather than serial hs-cTnT measurements. Furthermore, previous studies use a strategy whereby copeptin is measured in a blood sample acquired upon arrival at hospital. Considering the very early release of copeptin, measuring the biomarker as close to symptom onset as possible, preferably before the patient reaches hospital, improves the negative predictive values [20]. In contrast, troponin is ideally measured late after symptom onset owing to its late release from the damaged myocardium [18]. Results from the PreHAP (Pre-hospital diagnosis and triage of heart attack patients) trial demonstrated a potential for safe rule-out of AMI by the combination of pre-hospital copeptin and first in-hospital hs-cTnT [20].

No prospective studies have investigated the potential for LOS reduction and the safety of a rule-out strategy with optimal timing of blood sampling which combines pre-hospital copeptin levels with troponin levels measured upon admission. A large randomized controlled trial is needed to examine whether this accelerated rule-out strategy is a safe and reliable tool for rapid rule-out of AMI.

### Objectives

#### Primary objectives

Is early discharge based on the combined biomarker analysis associated with the following:Total duration of hospital stay?Time to decision regarding discharge or continued hospitalization?

Is early discharge based on the combined biomarker analysis associated with major adverse cardiac events (MACE) (*see* “Primary outcomes measures” section below)?

#### Secondary objectives

Is early discharge based on the combined biomarker analysis associated with early re-admission in patients with specific characteristics?Is early discharge based on the combined biomarker analysis associated with a change in patient experience, patient needs during and after admission, and mental health?Is early discharge based on the combined biomarker analysis cost-effective from a public perspective, regarding staff resources, costs of hospital stay, adherence to the labour market, and use of other health care services (cost-benefit analysis)?

#### Tertiary objectives

To evaluate the diagnostic performance characteristics of the accelerated rule-out algorithm as compared with standard diagnosticsTo evaluate the prognostic value of the accelerated rule-out algorithm as compared with standard diagnostics

### Hypothesis

We hypothesize that the combined measurement of pre-hospital copeptin and in-hospital high-sensitivity troponinReduces admission time by 12.5% in patients in whom AMI is ruled outReduces the time to decision of discharge or continued hospitalization in all patients suspected of AMIIs non-inferior compared with the standard rule-out procedure in relation to MACEIs cost-effective from an individual patient perspective and a public health system perspective

## Methods/design

### Aim

We aim to investigate the rule-out potential of copeptin measured in pre-hospital blood samples of patients suspected of AMI in combination with in-hospital hs-cTn compared with the standard rule-out protocol using consecutive in-hospital hs-cTn measurements.

### Study design

The AROMI (Accelerated rule-out of acute myocardial infarction using copeptin and troponin) trial is a randomized, controlled, open-labelled, multicentre trial with two parallel groups and LOS and MACE rate as primary endpoints. MACE rate is evaluated in a non-inferiority design.

### Setting

#### Study setting

The trial includes patients suspected of AMI who are admitted to a cardiac department at three different hospitals in the Central Denmark Region: two regional hospitals (Regional Hospital Central Jutland in Viborg and Regional Hospital in Horsens) and one tertiary highly specialized centre (Aarhus University Hospital in Skejby), which also functions as a regional hospital for its local catchment area. The study catchment area covers approximately 780,000 inhabitants and presumably 7500–8000 admissions/year with suspicion of AMI.

#### Danish health care system

The Danish health care system is governmental, financed by general taxes, free of charge for all patients. [21] The Danish health care system is divided into a primary sector consisting of general practitioners (GPs), private practice specialists, dentists, and physiotherapists and supportive care offered by the municipalities, and a secondary sector covered by public hospitals.

The GPs function as the patients’ primary contact and as gatekeepers to the rest of the health care system. In the Central Denmark Region, out-of-hours contacts are handled by a telephone and consultation service, provided by GPs or specially trained nurses. If needed, the out-of-hours service can refer the patient for hospitalization.

EMS is accessible via the emergency telephone number 1-1-2. EMS response for patients suspected of AMI includes an obligatory first tier of ambulance staffed with emergency medical technicians (EMTs) and/or paramedics and, for patients with respiratory or hemodynamic compromise, a second tier of ground-based, physician-staffed pre-hospital critical care teams or physician-staffed helicopter EMS in case of long-distance missions. All pre-hospital patient handling, diagnosis and treatment follows strict regional standard operating procedures.

Depending on the suspected condition, patients are transported to either 1 of the 21 EDs or to relevant specialized departments. Patients self-presenting at hospitals are in general rare in Denmark, probably owing to the high availability of primary-level care and EMS.

#### Admission and pre-hospital management of patients suspected of AMI in the Central Denmark Region

When suspicion of AMI is raised (by GP, out-of-hours service or EMS dispatch centre), patients are referred for hospitalization by ambulance. If the patients’ symptoms fulfil the EMS criteria for suspected AMI (defined as recent or ongoing prolonged symptoms of chest discomfort, new onset of dyspnoea in patients without prior pulmonary disease, or clinical suspicion of AMI), a venous blood sample is drawn for point-of-care (POC) analysis of cTn, and an electrocardiogram (ECG) is sent to the local cardiology department for interpretation. (Telemedicine conference between paramedic and cardiologist is performed via mobile telephone while the patient is still in the ambulance.) The cardiologist on call contacts the ambulance, and a tentative diagnosis is established, taking all available information (patient history, symptoms, transferred ECG and POC troponin) into account. Patients with relevant symptoms and risk factors for ischaemic heart disease or other cardiac causes are triaged directly to a department of cardiology for rule-in or rule-out of AMI or other relevant diagnostics and treatment. Patients with ST-elevation myocardial infarction (STEMI) or suspected high-risk cardiac conditions (including patients suspected of being at high risk of AMI, defined as patients with clear, characteristic symptoms of AMI and either significant ECG changes or elevated POC troponin) are triaged to a percutaneous coronary intervention (PCI)-capable cardiac centre. The remaining patients with miscellaneous symptoms and no risk factors are triaged to the ED.

Pre-hospital blood sample collection in patients suspected of AMI is a standard procedure in the Central Denmark Region. This provides a unique possibility to collect two separate timely blood samples at the time of admission.

### Participants

#### Inclusion criteria

Patients admitted by ambulance to a CCU on the basis of suspicion of AMI after having ECG diagnostics performed via telemedicineA successful pre-hospital blood sampling is required for inclusion.

#### Exclusion criteria

Aged younger than 18 yearsPatients in whom a firm and valid informed consent is unattainable (e.g., owing to psychiatric disease, dementia, under influence of euphoric substances)Patients triaged directly to the tertiary centre with suspected STEMI or for cardiac reasons other than suspected AMI (ventricular tachycardia, ventricular fibrillation, and third-degree atrioventricular block)Patients who, at the time of admission, are known to have central diabetes insipidusPatients in whom an obvious alternative diagnosis is suspected at the time of arrival to hospital (e.g., new supraventricular tachycardia, pulmonary embolism, aortic dissection) and without suspicion of AMI

At Aarhus University Hospital, patients are included only between 0800 and 2200 on weekdays (no inclusion on weekends or holidays). This is due to organizational procedures at the in-hospital central laboratory, which results in limitation of out-of-hours availability of copeptin analysis.

### Interventions

*See* Fig. 1) for the study SPIRIT figure and Fig. 3) for study flowchart.

**Fig. 3 Fig3:**
[figure not shown]
Study flowchart. Flowchart of patient courses in the two randomization groups. * Further diagnostic workup, including additional hs-ctn, is fully at the discretion of the attending physician. ** AMI is ruled out if both hs-ctn measurements are < 99th percentile URL or no significant rise or fall in hs-ctn is seen. *** AMI is ruled out if copeptin is < 95th percentile URL and hs-ctn < 99th percentile URL. *AMI* Acute myocardial infarction, *hs-ctn* High-sensitivity troponin, *URL* Upper reference limit

#### Intervention groups

Patients are randomized in a 1:1 allocation ratio into either of two diagnostics groups—the standard or accelerated diagnostic group—at the time of arrival to the hospital. “Standard” diagnostics follow the present standard diagnostic algorithm in Denmark, which is the European Society of Cardiology (ESC) 0 h/3 h algorithm. Patients have hs-cTn measured on arrival, depending on the result and the patient’s symptoms; hs-cTn is re-measured 3 h later. If both measurements are below the diagnostic cut point (the 99th percentile of healthy people), AMI is ruled out. The patient may then be discharged or receive further diagnostic workup or treatment for other conditions at the discretion of the attending physician.

The 0-h algorithm is not used in the Central Denmark Region, owing to patients’ difficulty in recalling changes in symptoms within the preceding 6 h. Thus, the majority of patients have at least two hs-cTn measurements performed.

“Accelerated” diagnostics include analysis of copeptin in a blood sample obtained in the pre-hospital phase and analysis of hs-cTn in a single blood sample drawn at the time of arrival at the hospital. All biomarker analyses are performed at the central hospital laboratory because POC instruments for pre-hospital copeptin measurement are not available.

If both makers are below the diagnostic cut-point (the 95th percentile of healthy people for copeptin and the 99th percentile of healthy people for hs-cTn), AMI is ruled out. The patient may be discharged or further diagnostic workup or treatment may be initiated at the discretion of the attending physician.

If either of the two biomarkers is above the mentioned cut points, AMI is not ruled out. Additional testing is decided by the attending physician. Unless alternative diagnoses are obvious, patients will have hs-cTn re-tested 3 h later as per the “standard” rule-out procedure.

#### Modifications

In both randomization groups, additional treatment and diagnostics (including repeat hs-cTn measurement) are fully at the discretion of the attending physician. Patients can withdraw from the study at any time point and will, if still admitted, follow the standard rule-out protocol (but without copeptin measurement, collection of extra blood samples or collection of blood samples for later use).

#### Adherence

All personnel are trained by local supervisors and are continuously reminded: 1) to follow the protocols for each randomization, and 2) regardless of randomization, to make a plan for the patient’s further course, taking the possible blood sample results into account. The written plan in the patient’s medical record could be as follows: ‘If troponin and copeptin/first and second troponin are normal, then…. If not, then…’.

### Concomitant care

#### Pre-hospital and in-hospital blood sampling

In the Central Denmark Region, all patients suspected of AMI have blood sampling performed by EMTs/paramedics in the ambulance before reaching hospital. The blood sample is drawn from a newly introduced peripheral venous catheter before flushing, using a blood collection tube with manually induced vacuum (Sarstedt Lithium-Heparin Coated S-Monovette, 5.5 ml; Sarstedt AG and Co., Nümbrecht, Germany). All tubes are labelled with a patient identifier (ID), date and time of collection. The blood sample is brought with the patient to the hospital, where it is collected by a central laboratory technician. The in-hospital blood samples are collected by the central laboratory technician according to local standard procedures and using standard tubes.

#### Handling of blood samples

The pre-hospital and first in-hospital samples are processed at the central hospital laboratory. Plasma is separated by centrifuging at 2500 *g* for 10 min and aliquoted into two samples for copeptin and hs-cTn analysis. The remainder of the copeptin sample is frozen at − 80 °C for storage in a biobank (*see* Additional file 2). Regardless of the patient’s randomization, the pre-hospital and first in-hospital samples are analysed for both hs-cTn and copeptin, but only results relevant to the assigned randomization are reported to the clinicians (*see* Fig. 1). Besides hs-cTnT and copeptin, a series of other analyses (e.g., white blood cell count, haemoglobin, lipid status, P-natrium, P-potassium, according to local procedures) are performed using the first in-hospital blood sample.

#### Additional in-hospital blood samples

Patients randomized to the standard diagnostic group will have a second (third if you count in the extra study sample; *see below*) blood sample taken after 3–6 h (*see below*). Patients randomized to accelerated diagnostics will only have a second blood sample drawn if copeptin, troponin or both are elevated in the initial blood samples or if requested by the attending physician. Second and later hs-cTn samples and analysis are performed as described above, except that copeptin is not analysed, and the remaining plasma is not stored. As a supplement, all patients in the standard diagnostic group will have an extra blood sample drawn 1 h after the first in-hospital blood sample. This sample is only analysed for hs-cTn, and no blood is stored. The extra sample is not drawn in the accelerated diagnostic group, because some of these patients potentially could be discharged at or before this time point.

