#### Sample request and reporting

Blood samples are requested by the personnel at the cardiac department according to the patient’s randomization status (for randomization process; *see below*). Requests for blood sample analysis are done by ordering pre-defined bundles/packages of analyses. This ensures that all patients have both copeptin and hs-cTnT measured in both pre-hospital and first in-hospital blood samples, but only results relevant to the randomization group are passed on to the clinicians, as follows:No copeptin results and no result of the 1-h troponin in the standard groupResults of pre-hospital but not in-hospital copeptin in the accelerated diagnostic group

All hs-cTn analyses are ordered with prioritization, meaning that the results have to be reported within 1 h.

Results are reported electronically from the hospital laboratory system (LABKA II; CSC Healthcare EMEA/DXC Technology, Boeblingen, Germany) to the clinicians via the electronic patient management system (Midt-EPJ; Systematic, Aarhus C, Denmark). All blood sample analysis results (including the blinded pre-hospital copeptin in the standard group and the in-hospital copeptin) can be retrieved from LABKA on request.

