##### Laboratory information management system

Data on blood sampling, including date and time of blood sampling, name and Nomenclature for Properties and Units code of the analyses, and results are retrieved from the laboratory information management system (LABKA).

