#### Manual adjudication

The manual adjudication is performed by an independent endpoint committee consisting of six to nine (depending on the final number of suspected events; *see below*) Danish independent cardiologists from outside the Central Denmark Region (*see* Additional file 4). Because of the high level of completeness and quality of the Danish health care registries and available electronic databases, a complete review of medical records from all patients is not considered to be necessary. Instead, only selected suspected events are presented to and evaluated by the endpoint committee (*see below*). Each suspected event is independently evaluated by two cardiologists. The adjudication is based on patient medical records, laboratory results and other supplementary information on request from the adjudicators. The endpoint committee is, per protocol, blinded to randomization status; the assigned group may be derived de facto from the medical record in most cases. All other information is available in the adjudication process.

All-cause death is accepted if the patient is registered as dead in the social security register. Survived cardiac arrest is accepted if a resuscitation attempt by a health care professionals is registered in the patient medical record and the patient survived to discharge. Non-scheduled re-vascularizing coronary intervention (PCI or CABG) is accepted if a non-scheduled coronary re-vascularization is registered in the patient medical record. Life-threatening, treatment-demanding arrhythmias are accepted if third-degree atrioventricular block, ventricular tachycardia or ventricular fibrillation resulting in initiation of treatment is registered in the patient medical record. Re-admissions with ACS (including NSTEMI types 1–5, STEMI types 1–5 and UAP) are accepted according to the criteria described in the Universal Definition of AMI (*see* Additional file 4 for full description). Myocardial injury is adjudicated by the endpoint committee but is not included as part of the endpoint of re-admissions with ACS.

The adjudication is documented in TrialPartner by each adjudicator, and the event is confirmed if both adjudicators agree. In case of disagreement between the two reported adjudications, the event is evaluated by a third member of the endpoint committee (*see* Additional file 4).

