#### Suspected events

A pre-adjudication is performed before endpoint committee assessment. Suspected events are automatically identified from all available data (*see* “Data materials” section) using STATA15 IC statistical/data management software (StataCorp, College Station, TX, USA).

Suspected events and automatic adjudication are defined for each possible endpoint of MACE. *See* the complete description of suspected events, MACE adjudication and automatic adjudication in Additional file 4.

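### The study-only 1-h troponin exists in the standard arm alone and, as written, is open to event detection and adjudication, so it can add ACS events to that arm only

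*Protocol article*

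**What the plan says.** All places are in the Protocol article.

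- **Who has the sample.** Under Additional in-hospital blood samples, "all patients in the standard diagnostic group will have an extra blood sample drawn 1 h after the first in-hospital blood sample". In the same section: "The extra sample is not drawn in the accelerated diagnostic group". On its use: "This sample is only analysed for hs-cTn, and no blood is stored".
- **Who sees the result.** Sample request and reporting withholds the 1-h troponin from the clinicians. It then adds: "All blood sample analysis results (including the blinded pre-hospital copeptin in the standard group and the in-hospital copeptin) can be retrieved from LABKA on request". The section Laboratory information management system names LABKA as a trial data source.
- **How events are found.** Under Suspected events: "Suspected events are automatically identified from all available data". That sentence points to the study's data list, which includes biochemistry results from the index admission.
- **What adjudicators receive.** Under Manual adjudication: "The adjudication is based on patient medical records, laboratory results and other supplementary information on request from the adjudicators". After stating that the committee is blinded to randomization status, the section continues: "All other information is available in the adjudication process".
- **What the value can affect.** ACS confirmed from randomization to day 30, including during the index admission, is a component of the primary MACE endpoint (Primary outcome measures, and the separate section on confirmed ACS). The Background says an AMI diagnosis needs a rising or falling biomarker pattern with at least one value above the 99th percentile.

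**The concern.** The 1-h sample guides no care. It is a research measurement taken in one arm and would not exist if either strategy were used in practice. A troponin value is nevertheless direct evidence for the ACS component of the primary safety endpoint. If the event-finding program or an adjudicator uses it, standard-arm patients have one more chance of being counted as an index-admission ACS than accelerated-arm patients have.

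Events added to the standard arm alone shrink the observed excess in the accelerated arm and so make non-inferiority easier to declare. For a safety endpoint, that is the unsafe direction. The Discussion already describes the 2% limit as a compromise and says a limit below 0.5% would be clinically most relevant, so there is little room for a hidden widening.

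A second, minor consequence is that a 1-h study troponin in a laboratory listing identifies the standard arm to an adjudicator who is meant to be blinded.

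**Working it through.** **1. The chain in the text**

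| Step | Section | Content |
|---|---|---|
| Value exists in one arm only | Additional in-hospital blood samples | Standard arm yes, accelerated arm no |
| Withheld from whom | Sample request and reporting | Clinicians; still retrievable from LABKA |
| Enters study data | Laboratory information management system; Baseline characteristics list | Results extracted; index biochemistry listed with no exception |
| Open to event search | Suspected events | All available data |
| Open to adjudicators | Manual adjudication | Laboratory results; everything but allocation |
| Bears on the endpoint | Primary outcome measures; Background | Index ACS counts; AMI rests on troponin change |

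No section removes the 1-h value at any step.

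**2. The plan's own sample size**

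Inputs from Sample size calculation: MACE 6.5% in both arms, limit 2 points, one-sided alpha 2.5%, power 80%; 1:1 allocation from Intervention groups.

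n per arm = (1.960 + 0.842)² × 2 × 0.065 × 0.935 / 0.02² = 2,385.1, rounded up to 2,386; total 4,772. This matches the stated figure exactly. At the planned 4,800 (2,400 per arm) power is 80.2%.

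**3. Effect of extra standard-arm events**

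The article gives no rate of ACS found only through the 1-h value. Let e be the assumed extra proportion of standard-arm patients who are counted as MACE only because of it. Patients who have another MACE within 30 days add nothing to e, because only the first event per patient counts.

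Take true rates of 6.5% (standard) and 8.5% (accelerated), so that the true excess equals the limit, with 2,400 per arm. The observed standard rate becomes 6.5% + e, and

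SE = √[(0.065 + e)(0.935 − e)/2400 + 0.085 × 0.915/2400]

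P(declare non-inferiority) = Φ(e/SE − 1.960)

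| e (points) | Extra events in 2,400 | SE (points) | e/SE | P(declare non-inferiority) |
|---|---|---|---|---|
| 0 | 0 | 0.760 | 0 | 2.5% |
| 0.1 | 2.4 | 0.762 | 0.131 | 3.4% |
| 0.25 | 6 | 0.766 | 0.326 | 5.1% |
| 0.5 | 12 | 0.772 | 0.648 | 9.5% |
| 1.0 | 24 | 0.783 | 1.277 | 24.7% |

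The limit in effect becomes 2.0 + e points. The SE must use 8.5% in the accelerated arm; putting 6.5% in both arms (SE 0.712 points) does not match the scenario and overstates the result, giving 5.4% at e = 0.25 and 29.0% at e = 1.0.

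**4. Which end of the range is plausible**

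Expected standard-arm MACE is 0.065 × 2,400 = 156. The top of the range, 24 events, would be 24/156 = 15% of these; the bottom is 2.4/156 = 1.5%. Most standard-arm patients have an arrival and a 3–6 h troponin either side of the 1-h one, and Handling of blood samples says the pre-hospital sample is analysed for hs-cTn in both arms. The 1-h value creates a new event only where the other samples miss the pattern, so the lower end is more plausible. It need not be zero: Intervention groups makes the 3-h repeat depend on the first result and the symptoms, and says only that most patients have at least two measurements. For the rest of the standard arm, the 1-h value may be the only later in-hospital one.

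**The case against.** **The full rules are elsewhere.** The complete definitions of suspected events and of manual and automatic adjudication are in Additional file 4, which is not shown and may already restrict which troponins count. This stands as a limit on certainty. It does not remove the point, because the article does more than leave a detail out: it positively admits all data and all information other than allocation.

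**The routing is not explicit.** Patient medical record and Registries are each named as sources for finding suspected MACE; the LABKA section is not. The ACS section relies on the national health registry, which would mainly reflect diagnoses by clinicians who never saw the value. This is fair and another reason to expect few extra events. But the event search refers to the data list that contains index biochemistry, and laboratory results are named for adjudication.

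**Extra detection is not shown.** A reader might infer that the 1-h sample does raise the standard-arm event count. The documents do not support that. They show that it can, and give no yield. ACS must also meet the Universal Definition criteria, and myocardial injury alone is excluded.

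**The larger imbalance is the missing 3–6 h sample.** A reader might count this too, since an accelerated-arm patient who is ruled out may have only one in-hospital troponin. That difference is part of the strategies being compared and no defect. Only the 1-h research sample lies outside them.

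**Unblinding is already conceded.** A reader might infer that the 1-h value is what breaks the blinding. Blinding says allocation will sometimes be evident, and Manual adjudication says it can be derived from the record in most cases. The 1-h value is one more marker, and a minor one.

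**Conclusion.** The point holds in a limited form. As written, a research-only troponin from one arm is open to both event detection and adjudication for a component of the primary non-inferiority endpoint. Any event it adds would fall in the standard arm and favour non-inferiority.

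The size is unknown and probably small. Under the assumed range of 0.1 to 1.0 points, the chance of declaring non-inferiority at a true 2-point excess rises from 2.5% to between 3.4% and 24.7%, with the lower end more plausible. These figures rest on the 6.5% and 8.5% rates, 2,400 per arm, a normal approximation, and no matching gain in the accelerated arm. They illustrate sensitivity and do not estimate what will happen. The text does not show that the comparison is in fact biased, and Additional file 4 may already close the gap. The change is worth making because it is cheap and the possible error runs in the unsafe direction.

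**What to change.** State under Manual adjudication and Suspected events that the 1-h hs-cTn is excluded from the laboratory extract used for suspected-event detection, for auto-adjudication and for the adjudicators' files, and that it is used only for its own diagnostic comparison. Confirm that Additional file 4 says the same; if it already does, one sentence in the article is enough.

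The exclusion should not be extended to all copeptin values. Pre-hospital copeptin in the accelerated arm is reported to clinicians through the electronic patient system, so removing it would mean redacting the clinical records that adjudicators read.

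The cost is a small programming change and the loss of one research value from adjudication. It needs no further patients, samples or visits.
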